## Abstract

**Background:**

Worldwide, minority youth receive culturally sensitive mental health services less often than the majority peer population. In Norway, limited research exists on the mental health and service use among youth from national minority (Forrest Finns, Kven or Norwegian Finns, Jews, Roma, and Romani), Indigenous (Sámi), and refugee backgrounds. Although the Norwegian government provides a public communication channel for youth, including mental health information and support, digital services have not been adapted to meet the needs of these groups. There is currently no research to determine the use, acceptability, effectiveness, cost-effectiveness, and safety of these services for these youth.

**Objective:**

The main aim of the *InvolveMENT* project is to improve the mental health of national minority, Indigenous, and refugee youth. The project’s objectives are, for these groups of youth, to (1) determine the mental health and digital support needs and possible barriers to and facilitators of service use; (2) assess the use of and satisfaction with digital services to meet their mental health needs; (3) explore their perspectives on digital mental health services; (4) develop recommendations that can be used to adapt digital services to meet their needs and rights; and (5) assess the use, acceptability, satisfaction, effectiveness, cost-effectiveness, and safety of adapted services.

**Methods:**

The 4-year *InvolveMENT* project consists of four phases: (1) establishing a longitudinal cohort consisting of national minority, Indigenous, and refugee youth, using surveys to assess their mental health, well-being, digital support needs, use and satisfaction with digital services, and possible barriers to and facilitators of service use; (2) conducting qualitative interviews with minority youth to explore their perspectives and synthesizing data from phases 1 and 2 for a mixed methods analysis; (3) involving youth and health care and other professionals to develop proposals to adapt and improve the existing digital services; and (4) a randomized controlled trial and a qualitative study to evaluate the adapted services.

**Results:**

Cohort and qualitative study designs have been completed. Ethics applications have been approved, and recruitment to the cohort and qualitative studies has started.

**Conclusions:**

The *InvolveMENT* project has the potential to enhance the accessibility and quality of health care services and early interventions, reduce inequality in service provision for minority groups, and strengthen collaboration between youth, public, and research organizations. Through this, it has the potential to improve the mental health of youth from these groups. The findings might be transferable to other minority groups, both nationally and internationally.

## Introduction

### Background

Approximately 10% of youth worldwide are diagnosed with mental disorders [1]. There are mental health disparities among minority youth internationally, and these are affected by social determinants of health that are influenced by factors such as socioeconomic status, access to education and health care, and experiences of discrimination [2]. Youth from Indigenous and national minority groups have poorer mental health than the general population. For example, a systematic review found that Indigenous populations had suicide rates 20 times higher than non-Indigenous populations, with the highest rates in youth aged 15 to 24 years [3].

The Indigenous population in Norway is the Sámi. There is limited knowledge about the mental health of Sámi youth. During the period from 1970 to 1998, suicide rates among Sámi youth were twice those of the majority youth population in Norway [4]. Internationally, asylum-seeking and refugee youth have high rates of mental disorders, such as posttraumatic stress disorder, anxiety, and depression [5-8]. In Norway, up to 42% of asylum-seeking and refugee youth have been found to fulfill the criteria for psychiatric disorders [9]. A recent review reporting on the mental health of the Roma population in Europe found a higher proportion of mental disorders among children compared to the majority population and limited access to mental health care [10]. There is, however, no knowledge about the mental health among youth who belong to the following five national minority groups: Forrest Finns, Jews, Kven or Norwegian Finns, Roma, and Romani [11].

### Mental Health Care Service Use Among National Minorities, Indigenous, and Refugee Youth

The mental health care needs of national minority, Indigenous, and refugee youth in Norway have only been assessed to a limited extent [9,11,12]. Service use may be low, and dropout rates may be high. There are cultural and language barriers, difficulties in developing trust, marginalization of minority groups, a lack of immigrant staff and interpreters, and ineffective care coordination [13,14]. Limited effort has been made to adapt services to meet their needs, despite the right to health pursuant to the International Covenant on Economic, Social and Cultural Rights (Article 12), which was made into Norwegian law in 1999. Although the Sámi Norwegian National Advisory Unit—Mental Health and Substance Use offers services to support the Sámi population, youth more often seek help from friends, partners, or family members [12,15], and scientific knowledge about their digital service needs is lacking. Apart from a single hospital-based mental health clinic, the Transcultural Centre at Stavanger University Hospital [16,17], no clinics in Norway specialize in or have adapted services to meet the mental health needs of asylum-seeking and refugee youth. Studies that focus on the different cultural backgrounds of youth (ie, culturally sensitive studies) are needed to determine how to develop services that are culturally relevant and appropriate to support minority youth [18-20].

### Digital Mental Health Care Services for National Minority, Indigenous, and Refugee Youth

Young people often use the internet to access information about mental health [21]. According to the technology acceptance model, youth are more likely to use digital services if they perceive them as both useful and easy to use. Moreover, trust in technology plays a central role in youths’ engagement with digital services [22]. Digital mental health interventions may facilitate service access for national minority, Indigenous, and refugee youth by addressing geographic, economic, and social disparities [23,24]. However, there is an evidence gap, and culturally sensitive, effective, and safe modes of digital health care delivery must be further developed and tested [24,25].

*DigiUng* is a Norwegian public cross-sectoral collaboration, run by the *Directorate for Children, Youth and Family Affairs* and the *Directorate of Health*. It has developed the public communication channel *ung.no* to provide information, health care, and support services for youth. However, these services have not been adapted to meet the mental health needs of national minority, Indigenous, and refugee youth, and there is no research evidence regarding their acceptability, effectiveness, cost-effectiveness, and safety for these groups.

### Aim and Objectives

The overall aim of the *InvolveMENT* project is to improve the mental health of national minority, Indigenous, and refugee youth. This will be done by adapting digital mental health services to meet their personalized information and support needs.

The objectives of the *InvolveMENT* project are to (1) determine mental health and digital support needs and the barriers to and facilitators of service use for national minority, Indigenous, and refugee youth; (2) assess the use of and satisfaction with digital services to meet the mental health needs of national minority, Indigenous, and refugee youth; (3) explore the perspectives of national minority, Indigenous, and refugee youth on digital mental health services; (4) develop recommendations that can be used to adapt digital services to meet the needs and rights of national minority, Indigenous, and refugee youth; and (5) assess the use, acceptability, satisfaction, effectiveness, cost-effectiveness, and safety of the adapted digital services to meet the support needs of national minority, Indigenous, and refugee youth.

## Methods

### Study Design

The *InvolveMENT* project uses a participatory, multidisciplinary, multiphase, mixed methods research design [26] to adapt digital mental health services to meet the mental health needs of national minority, Indigenous, and refugee youth in Norway. The four stages of the research include a cohort study (work packages [WP1]) to assess the needs, barriers, and facilitators of service use; qualitative studies (WP2) to explore the perspectives of youth from these groups on digital mental health services; co-design activities (WP3) to develop recommendations for adapting digital services; and an evaluation study (WP4) to assess the adapted digital mental health services through a randomized controlled trial (RCT) and a qualitative study.

The project will use the Trials within Cohorts (TwiCs) design to test the acceptability, effectiveness, cost-effectiveness, and safety of the adapted digital services in WP4. This design offers several advantages over conventional RCTs and quasi-experimental approaches, particularly in studies involving hard-to-reach populations. TwiCs design enables fast and efficient recruitment to the RCT, as participants are already enrolled in the broader cohort from which trial participants are selected. It helps to reduce attrition rates because individuals in the control group are not informed about interventions they are not offered, thereby minimizing disappointment bias. Moreover, by avoiding disclosure of unavailable treatments, the design enhances the generalizability of results, as participants’ expectations and behaviors are less likely to be influenced by knowledge of the intervention [27]. One-year rolling recruitment is used to compensate for natural attrition.

A participatory, multidisciplinary, multiphase, mixed methods design is particularly suited to complex health interventions, as it allows for the integration of diverse perspectives and methodological approaches. The participatory component ensures that youth voices are actively included throughout the research process, enhancing cultural relevance, acceptability, and ethical rigor. The multidisciplinary and multiphase structure enables the project to move iteratively from needs assessment to service adaptation and evaluation, ensuring that findings from each stage inform subsequent phases. Finally, the mixed methods approach provides both the breadth of quantitative data and the depth of qualitative insights, offering a more comprehensive understanding than any single method alone.

A participatory design approach is used to adapt digital services [23], involving national minority, Indigenous, and refugee youth and professionals working in health services, social services, and related sectors (eg, education). Close collaboration, cultural sensitivity, and empowerment of participants are used to develop strong partnerships and to ensure co-ownership. The project encourages and facilitates multisectoral collaboration between the services and support and interest organizations for national minority, Indigenous, and refugee youth; health care and service providers; and university-based research centers. The collaborative component with active involvement of youth strengthens the relevance of the research to meet the needs of these groups of youth. Youth representatives, representatives of health and service providers, health care workers, and co-researchers from minority groups are involved in all phases of the project, including planning, interpretation, and dissemination of results [28].

### Study Setting or Location

This national project involves youth and professionals in all 4 health regions in Norway. Online questionnaire surveys are carried out in the cohort study (WP1) and the RCT (WP4), facilitating participation of youth from different parts of the country. The locations for the qualitative studies (WP2) and co-design workshops (WP3) vary for the different minority groups but are spread throughout the country.

### Study Population

Throughout all phases of the project, participants will be recruited among youth who identify as belonging to at least one of the following groups: national minorities (Forest Finns, Jews, Kven or Norwegian Finns, Roma, and Romani), Indigenous Sámi youth, and refugees. In addition, in the first 2 of 3 cohort surveys (WP1), youth not belonging to the mentioned minority groups will be included. The inclusion of the broader group of youth will enable comparisons between minority and nonminority youth. During the co-design phase (WP3), professionals working in health and social services who engage directly with these youth groups will also be recruited.

In WP1, up to 1500 youth with minority backgrounds will be recruited for each of the 3 cohort surveys. Additionally, the first 2 cohort surveys will include up to 1500 youth who do not identify as belonging to the described minority groups. WP2 will include 50 to 100 youth from the different minority groups, ensuring representation across all groups. WP3 will involve a minimum of 50 youth and professionals. WP4 will recruit approximately 300 youth from the WP1 cohort for an RCT and 25 to 45 youth for a qualitative study based on their exposure to the adapted digital services, regardless of RCT participation.

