#### Randomization

In WP4, participants who meet the inclusion criteria will be randomly allocated in a 1:1 ratio using Microsoft Excel, either to receive the intervention (the adapted digital services) or to continue with usual care as part of the control group. Those assigned to the control group will not be informed that they are part of a trial or that other participants are receiving an intervention. This approach is consistent with the TwiCs design [27,33], which stages and tailors the consent process to reflect real-world clinical practice. The design ensures that individuals receiving usual care are not informed about treatments they will not be offered, thereby minimizing potential for disappointment bias.

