The evaluation study (WP4) will assess the implementation of recommendations developed in WP3 through two complementary procedures: an RCT and a qualitative study. The RCT will use the same survey instruments as WP1, with baseline data collected at the 6-month survey (before service adaptations) and follow-up data at the 18-month survey. The qualitative study will explore youth experiences with the adapted digital services, focusing on perceived support, safety, and satisfaction. Data will be collected through individual and focus group interviews depending on participants’ preferences. They will be conducted in participants’ preferred languages with professional interpreters as needed. Participants may include both RCT participants and others exposed to the adapted services. The number of participants will be guided by the concept of information power [43], with an estimated 25 to 45 participants. Interviews will be analyzed using qualitative content analysis [45], and findings will be integrated with RCT data through mixed methods analysis, applying triangulation to assess convergence, complementarity, and discrepancies [46].

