### Statistical Considerations and Data Analysis

#### Sample Size Calculation

Approximately 25% of youth are expected to experience mild to moderately severe symptoms of depression (PHQ-9 scores of 5‐19) [9,12,47]. To ensure a sufficient number of eligible participants for the RCT (WP4), a population cohort of 1500 youth will be recruited. This cohort size is designed to provide an adequate number of individuals who meet the inclusion criteria, which are scores of mild to moderately severe range on the PHQ-9, and to account for potential exclusions due to eligibility, nonconsent, or attrition. On the basis of an anticipated 20% dropout rate, 80% statistical power, a significance level of 0.05, and a moderate effect size of 0.35 (Cohen *d*), with equal allocation between intervention and control groups, the required sample size for the RCT is estimated to be 294. This has been rounded up to 300 to maintain sufficient power and accommodate potential variability.

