#### Data Analysis

Quantitative data analyses will be carried out for WP1 and WP4. In WP1, data analysis will include univariate analyses for descriptive statistics, whereas factors associated with service use will be assessed using correlation analyses, regression models, and multiple regression models to explore multiple predictors and adjust for confounders, for example, generalized linear models and linear and generalized additive models for nonlinear associations between predictor and outcome. Temporal changes will be assessed using mixed models to assess factors affecting service use.

To assess the use and acceptability of the intervention, that is, the adapted digital mental health services for youth, we will use data from the RCT to determine the proportion of participants who report using it. An intention-to-treat analysis will be used to test the effectiveness of the intervention offer, whereas an instrumental variables analysis will be applied to determine the effectiveness of the received intervention [48]. The primary outcome will be the PHQ-9 at 12 months of the trial. Subgroup analyses will be carried out for different minority groups. Results will provide data on variability in depression outcomes in the different groups. Safety will be assessed by determining the proportion of participants with deteriorated mental health status through higher PHQ-9 scores. Service satisfaction will be assessed using single-item questions, each targeting participants’ satisfaction with 1 of 8 different types of digital services. A cost-effectiveness analysis of the intervention for youth will be carried out by undertaking a cost-consequences analysis [49]. It will compare individuals taking advantage of the adapted services with those who do not. The analysis will take a societal perspective, relating costs associated with introducing the new interventions and attributable to youths’ mental health, school absence, and work productivity (if they are in work), as well as their quality of life.

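### The planning effect of 0.35 is not tied to the offer or to any assumed difference in use between arms, and the arm in which use is counted is not named

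*Protocol article*

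**What the plan says.** The existing service is run by a public collaboration: "It has developed the public communication channel" on which the adaptations will build (Digital Mental Health Care Services section). Eligible cohort members are randomised 1:1 to the adapted services "or to continue with usual care as part of the control group"; controls are not told of the trial (Randomization). Nothing is said about limiting their access.

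Exposure beyond the trial is anticipated. WP4 interviewees are chosen "based on their exposure to the adapted digital services, regardless of RCT participation" (Study Population), and elsewhere: "Participants may include both RCT participants and others exposed to the adapted services" (Data Collection, Interventions, and Follow-Up Procedures).

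Data Analysis separates the offer, tested by intention to treat (ITT), from the intervention received, estimated by instrumental variables. For use and acceptability, "we will use data from the RCT to determine the proportion of participants who report using it". Study Outcomes defines acceptability in the same way. Neither section names the arm.

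Sample Size Calculation uses "80% statistical power", a 0.05 significance level, 20% dropout, equal allocation and "a moderate effect size of 0.35". It arrives at 294, rounded up to 300. Measurement Tools describes the use items, shared by the cohort surveys and the RCT, as covering digital services.

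**The concern.** The analysis distinguishes being offered the services from using them, but the sample size does not. What is randomised is an offer, so the ITT contrast shrinks when some of those offered do not use the services or some controls do. The power statement can be interpreted only if the reader knows which effect 0.35 describes.

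Two measurement questions follow. The instrumental-variables analysis needs reported use of the adapted services in both arms, whereas the described items refer to digital services in general. The acceptability proportion needs a denominator: half of the randomised participants are deliberately not told of the service, so including them would understate uptake among those offered it. Acceptability is part of the project's fifth objective.

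**Working it through.** **Inputs from Sample Size Calculation:** d = 0.35, alpha 0.05, power 80%, 1:1 allocation, 20% dropout, stated N 294 rounded to 300. Sidedness is not given; two-sided is assumed. The article gives no rate of use for either arm, so every use difference below is an assumption.

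**Step 1. The plan's own figure.** The normal approximation gives n per arm = 2 × (1.96 + 0.84)² / 0.35² ≈ 128.1, so 129 per arm and 258 in total. Allowing for dropout, 258 / 0.80 = 322.5, so 323 (325 with the t-test). Multiplying by 1.20 instead gives 310 (312 with the t-test). A one-sided test gives 202, or 253 after dropout. None of these is 294. That figure appears only with dropout of about 12%: 129 / 0.88 ≈ 147 per arm.

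**Step 2. Power with no dilution.** 300 × 0.80 = 240 analysed, 120 per arm. 0.35 × √(120/2) = 2.711; 2.711 − 1.96 = 0.751; power = Φ(0.751) ≈ 77%.

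**Step 3. Dilution, if 0.35 is the effect of use.** Assuming the offer acts only through use, and nobody is put off using the services by being offered them:

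d(ITT) = 0.35 × (use in offered arm − use in control arm)

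| Assumed use difference | d(ITT) | Power, 120 per arm | N to randomise for 80% power, 20% dropout |
|---|---|---|---|
| 100% | 0.35 | 77% | 323 |
| 80% | 0.28 | 58% | 503 |
| 60% | 0.21 | 37% | 890 |
| 50% | 0.175 | 27% | 1,283 |

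**Step 4. The other reading, if 0.35 is the effect of the offer.** Power stays at 77%. The implied effect among users is 0.35 divided by the use difference: 0.35/0.80 = 0.44, 0.35/0.60 = 0.58, 0.35/0.50 = 0.70.

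**Step 5. The acceptability denominator.** With 1:1 allocation, 60% use in the offered arm and none among controls, pooling both arms gives (60 + 0)/2 = 30%. With 10% use among controls it gives (60 + 10)/2 = 35%.

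**The case against.** The strongest reply is that 0.35 is quoted for a comparison of two randomised arms, and that ITT is said to test the offer. The natural reading is then an offer effect, which already includes any dilution. That stands: a reader might infer that dilution has been shown to invalidate the power, but the article never says that 0.35 is the effect among users. What remains is that neither meaning is stated, that the offer reading implies a larger effect among users, and that power is 77% even on that reading.

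Other tempting inferences also go too far:

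- **Controls will be exposed.** The article foresees exposure outside the RCT; exposure of controls is inferred from a public channel with no described barrier. Implementation is left to service providers, so access is not yet fixed.
- **Adapted and ordinary use cannot be told apart.** The questionnaire is not shown, and Data Analysis expects participants to report using the adapted services. The description leaves it unclear whether a specific item exists; it does not show that one is missing.
- **The instrumental-variables analysis has the wrong first stage.** Nothing says that controls will be treated as unexposed, and the method can accommodate use in both arms.
- **Acceptability is pooled over arms.** The arm is simply unnamed. Acceptability is naturally judged among those offered the service, and an analysis plan could settle this.

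A practical objection also stands: asking controls about named adapted features could reveal the intervention that the design withholds from them.

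**Conclusion.** The concern holds as a failure to tie the effect size to what is randomised, together with an open denominator for uptake. The firm figure is 77% power at 300 randomised with 20% dropout, against the stated 80%; it requires only the article's own inputs and a two-sided test. The fall to 58%, 37% or 27% is conditional on 0.35 being the effect of use and on assumed use differences of 80%, 60% or 50%. On the offer reading, the same differences imply effects among users of 0.44, 0.58 or 0.70, which the article does not discuss. The halving of 60% uptake to about 30% is conditional on reading the denominator literally and on no use among controls. The point deserves action before the 18-month survey, because use that is not asked about then cannot be reliably recovered.

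**What to change.** 1. In Sample Size Calculation, state that 0.35 is the ITT (offer) effect, correct the stated power to about 77% at 300 randomised with 20% dropout, and show power over a range of between-arm use differences.
2. Ensure that the 18-month survey asks both arms about use of the adapted services, worded so as not to disclose the trial. Use the answer as treatment received in the instrumental-variables analysis, allowing for use among controls.
3. In Study Outcomes and Data Analysis, compute uptake and acceptability in the offered arm only, and report control-arm use separately as contamination.

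The cost is some wording, a few survey items, care in phrasing them for controls, and a less favourable stated power. Restricting access to the services is not needed for this fix.
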